We will assess the effectiveness of the S4R Toolbox through a cRCT (test case 1), a pre-post evaluation (test cases 2-4), and a cost-effectiveness evaluation (test case 1). In both study designs, the primary outcome will be health care workers’ mental well-being, measured using the SWEMWBS. Secondary outcome measures include individual resilience, organizational resilience capacities, burnout, turnover intention, self-assessed health, and, for informal caregivers, family involvement in care and caregiver self-assessment. In addition, sick leave will be assessed using public sick leave records where available. The effectiveness, cost-effectiveness, and cRCT analyses of the S4R intervention will provide information for decision makers in organizations at both the national and European Union (EU) levels.

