A 30% response rate was used as a conservative planning assumption for this pragmatic workforce trial in older adult care to reduce the risk of overestimating the effective sample size under real-world conditions. Participation and retention will be supported through leadership engagement, brief, mobile-friendly questionnaires, repeated reminders, and monitoring of response rates at each measurement time point.

The primary outcome measure, the SWEMWBS, will be treated as a continuous outcome. The primary analysis will follow the intention-to-treat principle at the home care service (cluster) level. Noncompliance with the intervention may attenuate the observed intervention effect. Linear mixed-effects models will be used, including random intercepts for clusters. Group (intervention vs control) will be included as a fixed effect, and SWEMWBS (mental well-being) will be the primary outcome. Other outcomes (burnout, turnover intention, caregiver burden, etc) will be analyzed as secondary end points.

Analyses will follow the intention-to-treat principle. A complier average causal effect analysis will also be conducted to account for variation in exposure to the intervention.

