#### Cost-Effectiveness Analysis

Cost-effectiveness analysis will be conducted only for the cRCT study design (Norway and Finland).

The primary outcome will be SWEMWBS, with effectiveness assessed using the same methods described in the previous section.

The costs of the intervention will be based on the time spent by leaders, health care workers, and researchers implementing the S4R Toolbox. The learning collaboratives support the leaders and are therefore expected to influence the effectiveness of the Toolbox. The cost data will be based on the following:

Minutes that health care workers use the Toolbox (data source: log files from the digital Toolbox).Hours that leaders and health care workers spend in meetings discussing the themes of the Toolbox and planning deimplementation or other workplace changes (data sources: learning collaborative meetings and interviews with leaders).Hours that leaders and researchers spend participating in local learning collaboratives (data source: notes/minutes from the learning collaboratives, including time and participants).The time spent by health care workers, leaders, and researchers will be valued using nationally representative wages and social security contributions.

The time horizon for the analysis is 1 year; therefore, no discounting will be applied. The analysis adopts the perspectives of 2 funders: the participating organizations, which cover the costs of leaders’ and health care workers’ time, and the S4R project funding organization (EU), which covers the costs of researchers’ support for implementing the Toolbox.

We use intention-to-treat based analyses and evaluated the incremental net monetary benefit of the Toolbox compared to no Toolbox ("practice as usual"). We evaluated incremental net monetary benefit (NMB) in comparing the alternatives. NMB is calculated by multiplying the observed effects by the decision-makers’ willingness to pay, λ, for an extra unit of effectiveness, and then subtracting the observed cost [37,38]. As the willingness to pay for one extra unit of effectiveness in SWEMWBS is unstated, we use a range of values.

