As a sensitivity analysis, we will use an algorithm to convert changes in SWEMWBS scores into WELLBY (Wellbeing-Adjusted Life Year) units [39-41]. WELLBYs have been monetized and can therefore provide a monetary estimate of effectiveness. This analysis will also provide an opportunity to interpret the results of the cost-effectiveness analysis across the range of willingness-to-pay values.

To further support the robustness of our analysis, we will also conduct a cost-benefit analysis. For this analysis, we will collect data from the participating organizations (work units) on sickness absence (spells and days), staff resignations, turnover, disability pensions, and personnel survey results for the years 2023-2026. Where possible, these measures will be monetized using national recommendations, statistics, reports, and research.

The S4R project does not aim to estimate a single pooled effect across countries. The participating health care systems differ substantially in structure, governance, workforce composition, and the availability of formal older adult care services. Because of this heterogeneity, the project follows the MRC guidance for evaluating complex interventions, which explicitly recommends that evaluation designs be adapted to local feasibility and contextual conditions.

In Norway and Finland, organizational structures allow randomization of home care units, making a cRCT feasible and appropriate for evaluating both effectiveness and cost-effectiveness. In the other participating countries, randomization was not feasible because of organizational differences and the absence of comparable units. For these countries, a pre-post evaluation is methodologically appropriate and enables examination of within-country change. This hybrid approach preserves scientific rigor by using the strongest possible design where feasible while ensuring validity and contextual relevance across diverse older adult care systems.

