### Organizational-Level Approaches to Resilience

Traditionally, resilience and well-being interventions in health care have focused predominantly on individual-level strategies [11,18,19]. Although such approaches may provide short-term benefits, organizational-level interventions are more likely to generate sustainable, system-wide effects [11,47]. The S4R Toolbox therefore prioritizes strengthening organizational resilience as a structural pathway to improving individual resilience and mental well-being.

Evidence suggests that organizational resilience shapes how health care workers respond to stress and adapt to work-related challenges [48-50]. By targeting organizational structures, governance mechanisms, leadership practices, and coordination processes, the S4R intervention seeks to create enabling conditions that support both individual and collective resilience.

The Toolbox is designed to enhance leaders’ access to evidence-based knowledge about the needs of workers and informal caregivers, as well as organizational functioning. By facilitating informed leadership practices, it may strengthen resilience and promote supportive work environments. If effective, such changes could contribute to improved job satisfaction and workforce retention, which are critical challenges in older adult care.

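### The cRCT collects recorded resignations and turnover only for a supporting cost-benefit analysis; the one named retention-related effectiveness outcome is self-reported turnover intention

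*Protocol article*

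**What the plan says.** The Overview of the Implementation, Evaluation, and Finalization Phase makes SWEMWBS the primary outcome and continues: "Secondary outcome measures include individual resilience, organizational resilience capacities, burnout, turnover intention, self-assessed health". It adds two informal-caregiver measures, and sick leave from public records where these exist. The cRCT section repeats the list in short form: "Other outcomes (burnout, turnover intention, caregiver burden, etc". Turnover intention is a questionnaire measure (section on Resilience and Mental Well-Being Factors).

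Recorded exits appear in the Cost-Effectiveness Analysis section. For the cost-benefit analysis, the participating work units are to supply data on "sickness absence (spells and days), staff resignations, turnover, disability pensions, and personnel survey results for the years 2023-2026". That analysis has a supporting role: "To further support the robustness of our analysis, we will also conduct a cost-benefit analysis". The stated handling of the data is: "Where possible, these measures will be monetized using national recommendations, statistics, reports, and research". The section applies to the randomized part only: "Cost-effectiveness analysis will be conducted only for the cRCT study design (Norway and Finland".

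Retention is part of the problem described in the Introduction. It returns in the Discussion as a possible consequence if the Toolbox works: "such changes could contribute to improved job satisfaction and workforce retention, which are critical challenges in older adult care".

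**The concern.** The trial plans to hold both a stated intention and the event that the intention stands for. Only the intention is named as an effectiveness outcome. Three features make it the weaker of the two here.

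- **Response.** Planning assumes that 30% of workers answer. Those who answer may differ from those who do not.
- **Leavers.** A worker who resigns may well stop answering later waves, so the measure is likely to be missing in the people who had the event. The main missing-data method assumes missing at random; pattern-mixture approaches appear only as a sensitivity analysis.
- **Awareness.** Staff work through the Tool 2 modules with their leaders, so intervention-arm respondents know about the programme when they report their intentions.

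Work-unit records are less exposed to all three. The protocol already accepts records as effectiveness evidence for sick leave and gives no reason for treating exits differently. Without a named comparison, a favourable difference in exits could be brought forward afterwards, or an unfavourable one left inside a monetized total. The project promises recommendations to policy makers, who are likely to ask about retention.

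**Working it through.** **1. Where each measure is used**

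| Measure | Source | Named use |
|---|---|---|
| Turnover intention | Questionnaire | Secondary effectiveness outcome |
| Sick leave | Public records where available | Effectiveness outcome |
| Sickness absence | Work units | Cost-benefit analysis |
| Resignations, turnover | Work units | Cost-benefit analysis only |

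Sickness absence has a record-based counterpart among the effectiveness outcomes. Exits have none.

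**2. The plan's own power figure**

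The only power statement for the cRCT is d=0.28-0.32 for mental well-being at 95% power. Inputs from the cRCT section: 30 clusters, 1:1 allocation, 9 respondents per cluster, ICC 0.05, six measurements, within-person correlation r = 0.5-0.7. Two-sided alpha of 0.05 is assumed.

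- Respondents per arm: 15 × 9 = 135. Design effect: 1 + 8 × 0.05 = 1.40. Effective number: 135/1.40 = 96.4.
- Variance factor for the mean of five follow-ups adjusted for baseline: (1 + 4r)/5 − r², which is 0.35 at r = 0.5 and 0.27 at r = 0.7.
- d = (t₀.₉₇₅,₂₈ + t₀.₉₅,₂₈) × √(2 × factor/96.4) = 0.319 and 0.281.

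The stated range reproduces, but it says nothing about turnover.

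**3. Precision for recorded exits**

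Assumptions not in the document: yearly exit rate p of 10-25%, ICC for exits of 0.01-0.05, and records covering all of about 30 workers per cluster, that is 15 × 30 = 450 per arm. Expected exits over a full year are then 45 to about 113 per arm.

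Design effect DE = 1 + 29 × ICC, which is 1.29 at ICC 0.01 and 2.45 at ICC 0.05. The 95% half-width for the arm difference is t₀.₉₇₅,₂₈ × √(2p(1−p) × DE/450), with t = 2.048.

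| p | ICC 0.01 | ICC 0.05 |
|---|---|---|
| 10% | ±4.7 points | ±6.4 points |
| 25% | ±6.7 points | ±9.3 points |

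This takes no credit for adjusting for each unit's earlier rate.

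**4. Power, for orientation**

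With the effective number per arm at 450/2.45 = 184 (ICC 0.05) or 450/1.29 = 349 (ICC 0.01), and control rates of 10-25%:

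| Relative reduction | ICC 0.05 | ICC 0.01 |
|---|---|---|
| One third | 21-49% | 35-77% |
| One half | 44-87% | 71-99% |

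**5. Record window**

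Implementation is scheduled to begin in April 2026 (Results section) and is planned to take 12 months (S4R Intervention Design Development Phase), so it runs to about the end of March 2027. Records to December 2026 cover about 9 of the 12 months and miss about a quarter. The same gap affects the cost-benefit analysis, since the economic evaluation has a 1-year horizon.

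**The case against.** The strongest reply is that nothing here is a contradiction. The objectives and the effectiveness question in Table 1 concern resilience and mental well-being; retention is background in the Introduction and a conditional remark in the Discussion. The Literature Reviews section classes turnover with economically relevant outcomes, so placing it in the economic evaluation is consistent. The outcome lists are open-ended, and the full protocol and SAP are not shown. All of this stands. It makes the point an improvement to a design choice and leaves the protocol free of internal conflict here.

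A reader might go further and infer that turnover intention is the trial's only effectiveness outcome, or that the trial cannot say whether the Toolbox keeps staff. The document supports neither. SWEMWBS, individual resilience, organizational resilience capacities, burnout, self-assessed health and sick leave are also effectiveness outcomes. A cost-benefit analysis of Toolbox against no Toolbox needs an arm difference in exits, so an estimate could emerge from it. What is absent is a named comparison with a stated analysis.

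Two further replies also stand. The article does not say that the records cover every employed worker or use one definition of turnover in both countries. And precision is low, so naming the outcome would not by itself settle the retention question.

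**Conclusion.** The point holds as an improvement worth making. Recorded resignations and turnover have a stated use only in a supporting economic analysis, and the named retention-related effectiveness evidence is a self-report from planned respondents of about 135 per arm, likely to be missing in leavers. The likelihood that leavers stop responding is a judgement; the article does not say how they are followed.

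Naming the recorded rate would yield an estimate with a 95% interval of roughly ±5 to ±9 percentage points. This rests on assumed exit rates, an assumed ICC, full coverage of about 450 workers per arm and a full year of records. The planned record window does not supply that full year, so the intervention-year rate cannot be computed from the data as planned.

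**What to change.** Unless the full protocol or SAP already does so, and before exits by arm are seen:

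1. Name the resignation/turnover rate from work-unit records as a secondary or exploratory cRCT outcome. Compare arms as randomized at cluster level, with the unit's pre-intervention rate (records start in 2023) as covariate. Report the difference with its 95% interval.
2. Extend the records beyond 2026 to the end of the 12-month intervention. Failing that, state that the outcome, and the turnover input to the cost-benefit analysis, covers only about the first 9 months.
3. Set one definition of turnover for Norway and Finland, and state which workers the records cover.
4. Keep turnover intention as a separate self-reported outcome.

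The cost is one outcome entry, one cluster-level model, about three more months of records, and agreement on a definition. The price in interpretation is an imprecise estimate, which should be presented as such.

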### Co-Design of the S4R Toolbox and Prototype Testing Phase

#### Overview

The second phase (WP3) will lead to the development of a digital S4R Toolbox for leaders to promote resilient performance and mental well-being among health care workers and informal caregivers. WP3 begins in month 5 and continues through month 30. The features and content of the S4R Toolbox will be developed based on findings from the first input phase, systematic literature reviews, and cross-country qualitative and quantitative data collection. Cross-country data from diverse settings will be used to provide an understanding of factors and challenges that are relevant across settings (residential care homes, home care services, and the hospital-to-home interface) and target groups (leaders, health care workers, and informal caregivers), ensuring that the S4R Toolbox provides value across the included older adult care settings. The development phase applies an iterative co-design methodology using an Agile software development process [33], in which a development team continuously develops the content and features of the S4R Toolbox by organizing 8 collaborative workshops (6 national and 2 transnational) with a co-design panel consisting of consortium partners and collaborators, as well as representatives of the target groups (3-5 health care leaders, 3-5 health care workers, and 3-5 informal caregivers), to ensure relevance and usability.

The S4R Toolbox includes 3 tools: (1) Mapping and Identification Tool (to increase awareness), (2) Reflection and Education Tool (to increase understanding), and (3) Reorganization Tool (to support reframing; Figure 1). While the S4R Toolbox is intended for leaders, the tools rely on the involvement of different stakeholders, including health care workers and informal caregivers, to ensure collaboration across organizational levels and stakeholder groups. All test sites will implement and evaluate the S4R Toolbox through a 1-year intervention program. The S4R Toolbox aims to bring about organizational- and system-level changes through leaders as change agents to improve working conditions for frontline health care workers and informal caregivers. Accordingly, the intervention requires sufficient time for these changes to take place.

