#### S4R Intervention Design Development Phase

Given the pace of work and the stressful environment of older adult care, the intervention design will be aligned with everyday work to reduce the likelihood that leaders will perceive the intervention as an additional stressor [34]. The S4R intervention will consist of 3 phases, each corresponding to 1 of the 3 tools in the S4R Toolbox. During each phase, frontline leaders will engage with different elements of the tool and participate in different activities (see Multimedia Appendix 3). The implementation of the intervention is planned to take 12 months. Six local learning collaboratives (including consortium researchers and co-researchers from the clinical setting) will be established, 1 in each European partner country, in addition to 1 principal learning collaborative comprising representatives from all 6 local learning collaboratives. Australia will have a separate learning collaborative because of time zone differences.

For each country, a designated intervention team consisting of consortium partners will be formed. The teams will be responsible for administering the local learning collaborative and coordinating the overall implementation activities throughout the intervention in their respective countries.

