### Implementation, Evaluation, and Finalization Phase

Full implementation of the S4R Toolbox in 6 European countries (Norway, Finland, Italy, the Netherlands, Romania, and Spain) and Australia is scheduled to begin in April 2026. Preparatory work has included the development of the implementation plan (see Multimedia Appendix 4) and supporting materials for the workshop-based intervention. For the cRCT, intervention and control sites have been randomized and are ready for study initiation.

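### The records for the supporting cost-benefit analysis stop at the end of 2026, three to four months before the 12-month intervention ends

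*Protocol article*

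**What the plan says.** The Cost-Effectiveness Analysis section of the protocol article describes three economic analyses for the cluster randomized trial in Norway and Finland: a main analysis of incremental net monetary benefit on the SWEMWBS, a sensitivity analysis that converts SWEMWBS changes to WELLBYs, and a cost-benefit analysis added to support robustness.

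For the last of these, the work units supply figures on absence through sickness, on staff who resign and on turnover, together with "disability pensions, and personnel survey results for the years 2023-2026". The measures are to be monetized where that can be done.

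The same section gives one horizon, "The time horizon for the analysis is 1 year; therefore, no discounting will be applied", and one definition of costs: "The costs of the intervention will be based on the time spent by leaders, health care workers, and researchers implementing the S4R Toolbox".

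The dates stand elsewhere:
- Results, Implementation, Evaluation, and Finalization Phase: the roll-out, with Norway and Finland among the countries listed, "is scheduled to begin in April 2026".
- Methods, S4R Intervention Design Development Phase: "The implementation of the intervention is planned to take 12 months".
- Methods, Overview of the co-design phase: "All test sites will implement and evaluate the S4R Toolbox through a 1-year intervention program".

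**The concern.** A record window that closes on 31 December 2026 cannot cover a 12-month intervention that begins in April 2026. No section extends the records into 2027, and none ends the costs in December 2026.

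The cost-benefit analysis is the planned analysis that puts a money value on absence and turnover. If implementation costs are counted for the whole year while these outcomes are counted for only part of it, the two sides of the balance refer to different periods. Randomization does not repair this. Both arms share the short window, so the contrast within 2026 is valid but incomplete, whereas the cost of implementing the Toolbox falls on one arm only. The co-design Overview also says that the organizational changes need time, so the later months of the intervention year are not ones to lose lightly.

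**Working it through.** **Inputs**
- Record window: 2023-2026, so the last covered day is 31 December 2026 (Cost-Effectiveness Analysis).
- Start: April 2026, day not given (Results, Implementation, Evaluation, and Finalization Phase). Norway and Finland are among the countries named.
- Duration: 12 months (S4R Intervention Design Development Phase; co-design Overview).
- Horizon: 1 year (Cost-Effectiveness Analysis).
- Evaluation work package WP4: project months 22-43 (Methods, Implementation, Evaluation, and Finalization Phase, Overview). Progress is reported at month 23 of 48 (Interim Report and Study Progress).

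**Step 1: can the window supply the stated 1-year horizon?** Counted in whole months, April 2026 plus 12 months runs from April 2026 through March 2027. April to December 2026 is 9 months, and January to March 2027 is 3. Coverage is 9/12 = 75%, so the 1-year horizon is not reached.

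**Step 2: how much does the day in April matter?** Covered days run from the start to 31 December 2026, out of 365.

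| Start | Days covered | Share | Months covered | Days missed |
|---|---|---|---|---|
| 1 April 2026 | 275 | 275/365 = 75% | 9.0 | 365 - 275 = 90 |
| 30 April 2026 | 246 | 246/365 = 67% | 8.1 | 365 - 246 = 119 |

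The window covers 8.1 to 9.0 months and misses about 3 to 4.

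**Step 3: is the cost side cut to match?** The cost sources are Toolbox log files, meetings, interviews with leaders and learning-collaborative notes. None has an end date. The only period given is the 1-year horizon, stated for the cost-effectiveness analysis and not repeated or changed for the cost-benefit analysis. That the cost-benefit analysis uses the same costs and horizon is an inference, but the section offers no other.

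**Step 4: what if the records are calendar-year totals?** The article does not say how fine they are. If they are annual, the 2026 figure mixes at least 3 months before the start (January to March) with the intervention months.

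**Step 5: is there room to extend?** The project begins in 2024. The report at month 23 still describes the April 2026 start as planned, so month 23 is taken to be April 2026 at the latest. That puts project month 1 no later than June 2024. Month 43 then falls between July 2027 (start January 2024) and December 2027 (start June 2024). The 12-month point, at the end of March to the end of April 2027, lies before that in every case.

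**The case against.** The strongest reply is that little depends on this analysis. The main economic result uses the SWEMWBS over one year, the sensitivity analysis converts those same scores, and the trial's primary outcome is the SWEMWBS. None uses these records. Sick leave as a secondary outcome comes from public records, for which no 2026 limit is stated. All of this stands and confines the point to the supporting analysis.

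It can also be said that the article never states a cost window for the cost-benefit analysis, and that log files and dated meeting notes would let much of the cost be limited to 2026. That is correct. It makes the mismatch a plain reading rather than an explicit statement, and it provides a fallback remedy. It does not bring the outcome data up to one year.

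A reader might infer more than the documents support:
- **A certain bias against the Toolbox.** The direction depends on the Toolbox reducing absence or turnover, which is what the trial is to find out.
- **A definite loss of benefit.** A benefit constant by month would be captured at 9/12 = 75%. One rising linearly by month would be captured at (1+...+9)/(1+...+12) = 45/78 = 58%. Both curves are assumptions; the article gives none.
- **A figure for the third tool.** The lengths of the three phases are not in the text at hand, so no share of the last phase can be computed.
- **A fault in having no follow-up after the intervention.** The 1-year horizon is a stated choice, and the limitations section says that funding restricts the evaluation period.

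**Conclusion.** The point holds in a narrow form. The stated record window ends 3 to 4 months before the 12-month intervention does and covers about 8 to 9 of its 12 months (67% to 75%). This follows from the article's own dates and assumes only that implementation starts in April 2026 as scheduled.

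That a full year of cost would be set against this shorter span rests on one inference: that the section's only horizon and cost definition also apply to its cost-benefit analysis. If so, and if the Toolbox lowers absence or turnover, net benefit would be understated by an amount that cannot be fixed from the documents. The error is confined to the supporting analysis and gives no ground for doubting the main cost-effectiveness result.

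**What to change.** In the Cost-Effectiveness Analysis section, replace the 2023-2026 window with one that runs from 2023 through the end of the 12-month intervention (March or April 2027, depending on the start day), in both arms. Ask for records fine enough to separate the months of 2026 before the start from the intervention months. State the horizon of the cost-benefit analysis explicitly.

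If 2027 records cannot be obtained, restrict the costs to the months that the outcome data cover and state the shorter horizon. The two sides would then match, but the analysis would no longer describe the full intervention year, and hours reported in leader interviews may be harder to date than log files or meeting notes.

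The cost is three to four more months of the same administrative data and slightly later delivery, within WP4. Extending to all of 2027 is not needed: it would exceed the 1-year horizon on which the absence of discounting rests, and could run up to or past the end of WP4.
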